**Figure 3 Fig3:**
[figure not shown]
**Procedures for data collection and management in the SILVER-AMI study.** Data collection and management involves a coordinated effort between study sites and Yale Coordinating Center.

### Six-month interview

The six-month telephone interview is conducted by staff at the Yale Coordinating Center. For participants with impaired decisional capacity at baseline, the six-month interview is completed with both the participant and assigned proxy.

The six-month interview repeats several key components of the baseline interview (Table 2), including questions about both general and disease-specific health status. In addition to the outcomes of re-admission and death, we define a decline in health status as a 10% reduction in overall quality of life as measured by the SF-12 [25]. Participants are also questioned on whether they have been re-hospitalized, and whether they have experienced any signs or symptoms that they attribute to medications (i.e., “adverse effects”) since their AMI discharge. If present, the participant is asked the medication to which they attribute the symptoms and if any action was taken to address the adverse effect. Participants receive an additional $50 gift card for completing the six-month interview.

### Events review

At the six-month time point, the site research coordinator collects medical records on any hospital readmissions, outpatient cardiac procedures, emergency department (ED) visits, and deaths from the index hospital, as well as all other hospitals the participant reported using at the time of baseline interview. Medical records are provided to the Yale Coordinating Center where the events are reconciled with the participant’s self-reported hospitalizations during the 6-month phone interview. Any outstanding records are then collected. Medical records and death certificates are reviewed by physician investigators to determine whether the reported events represent true hospital admissions, as well as the primary discharge diagnosis, and/or cause of death.

### Data management

The baseline interview is completed by the site research coordinator and transmitted electronically to the Yale Coordinating Center within three days (Figure 3). A Yale research assistant reviews the form and queries the site for missing or incomplete items. The site also transmits medical records, including emergency department and inpatient notes, ECGs, cardiac catheterization and operative (CABG) reports, and echocardiogram results, for abstraction by a research nurse at the Yale Coordinating Center.

All study data are managed at the Yale Coordinating Center using REDCap, an NIH-supported, HIPAA-compliant web-based Electronic Data Capture (EDC) system [26]. A custom Site Portal website manages the various administrative and scientific site workflows, including: site enrollment, IRB tracking; study document distribution, staff training, participant enrollment, invoicing, and site performance monitoring. In addition, we have integrated REDCap’s error detection and resolution features into a Data Query Quality Control system (DQCQ) that allows for error checks of varying complexity using SAS programs.

### Statistical analysis

The primary outcomes of SILVER-AMI are the occurrence of all-cause hospital readmission, all-cause death, and decline in health status within six months of hospital discharge. Using independent risk factors that include cardio-centric factors (e.g. STEMI vs. NSTEMI, systolic blood pressure, Killip Class), as well as geriatric impairments, we will construct risk stratification models that predict the probability of each outcome for specific combinations of the risk factors. These models will be variants of the Cox regression models for the time-to-event outcomes (hospital readmission and mortality) and the logistic model used for decline in health status. Because mortality serves as a competing risk for hospital readmission, we will evaluate the associations of explanatory variables with both time-to-event outcomes using the competing risk approach of Fine and Gray [27]. All linearity assumptions will be checked graphically and deviations from model additivity will be accommodated by an examination of all statistically significant, clinically indicated two-factor interactions. All missing data will be examined for the nature of missingness, i.e., whether missing at random, and if justifiable, multiple imputation will be applied. Models will be evaluated with an examination of residuals and goodness-of-fit statistics using SAS/STAT ® V9.3 (SAS Institute, Cary, NC) or later, with statistical significance defined as a two-sided p-value <0.05.

Internal and external validation techniques will then be used to test the reproducibility of the risk stratification tools. For internal validation, jackknife methods [28] will be used to evaluate the percent of correct classification; external validation will be performed on the 500 randomly selected participants who were excluded from both model building and internal validation.

Once the final models have been developed, user-interface applications will be developed for “smart-phones” and other hand-held devices. The model coefficients for each outcome will be stored in hand-held applications whose outputs will provide the probability of each outcome. The inputs to the applications will consist of simple yes/no entries denoting the presence or absence of risk factors. Calculation will be presented in real time, and the results will list specific risk factors, and probability of the outcomes.

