### Sample size and power

Of the SILVER-AMI cohort of 3000 participants, 2500 participants will serve as the development cohort and 500 will be randomly selected as the validation cohort. Based on 2008 Medicare data, we posited outcome rates of 39% and 28% for all-cause readmission and mortality. Based on previous research [29], we also assumed that a 10% decline in health status, as measured by the SF-36, would occur in 35% of surviving participants. With regard to the explanatory variables of primary interest, i.e., geriatric conditions and socio-demographic and clinical factors, we assumed each would exhibit measures of relative risk ≥1.3 for each time-to-event outcome and ≥1.5 for decline in health status. The 2500 participants in the development cohort provide 90% power to detect the stated magnitudes of relative risk for prevalence of the explanatory variables between 30% and 50%. For the validation sample, the accepted standard for time-to-event and logistic models should be large enough to contain a minimum of 100 outcome events [30]. For mortality, the least frequently expected outcome, the additional sample of 500 should allow for 140 events. The validation size of 500 will be preserved regardless of overall mortality and dropout.

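### Internal validation is scored only by percent correct, does not say that model selection is repeated, and is followed by storing coefficients without stated shrinkage

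*Protocol article*

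**What the plan says.** All of this is in the Statistical analysis section of the protocol article, except the cohort sizes.

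- **Model building.** Models are made "Using independent risk factors that include cardio-centric factors" and geriatric impairments. For interactions, "deviations from model additivity will be accommodated by an examination of all statistically significant, clinically indicated two-factor interactions", with "statistical significance defined as a two-sided p-value <0.05". No rule for selecting main effects and no number of candidates is given.
- **Order.** "Internal and external validation techniques will then be used to test the reproducibility of the risk stratification tools".
- **Internal validation.** "For internal validation, jackknife methods [28] will be used to evaluate the percent of correct classification". No other measure is named for this step.
- **Held-out sample.** "external validation will be performed on the 500 randomly selected participants who were excluded from both model building and internal validation". Sample size and power gives the split: "2500 participants will serve as the development cohort and 500 will be randomly selected as the validation cohort". It expects 140 deaths among the 500.
- **Use of the result.** "The model coefficients for each outcome will be stored in hand-held applications whose outputs will provide the probability of each outcome". No shrinkage or recalibration is mentioned before storage.

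**The concern.** Two things look weak.

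First, the measure. The Background section hypothesises better discrimination than existing risk models, and the product is a tool that displays probabilities. Percent correct measures neither discrimination nor calibration, and it responds little to overfitting when most patients have no event.

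Second, the object being validated. The section builds the models, then tests the finished tools. If the factors and interactions chosen on the full development cohort are kept fixed in every leave-one-out fit, the jackknife allows for estimating the coefficients but not for having chosen the terms on the same data. The internal result would then look better than the tool will perform. Because the coefficients are stored as fitted, displayed risks would tend to be too high for high-risk patients and too low for low-risk patients, with nothing in this step to show it.

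**Working it through.** **1. The plan's own figures.** Development deaths: 2500 × 0.28 = 700. Validation deaths: 500 × 0.28 = 140, as the article states.

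**2. What percent correct can show.** A rule that calls everyone event-free scores 1 − event rate:
- death: 1 − 0.28 = 72%
- readmission: 1 − 0.39 = 61%
- decline, among survivors: 1 − 0.35 = 65%

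The sampling error of percent correct near 72% is √(0.72 × 0.28 / 2500) = 0.9 points in the development cohort and √(0.72 × 0.28 / 500) = 2.0 points in the held-out sample.

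**3. Size of the optimism if the terms are held fixed.** The article gives no candidate count, so the settings below are assumptions: 2500 participants, 28% events, a logistic model, yes/no candidates with 35% prevalence, backward elimination at p<0.05, and classification at a predicted risk of 0.5. The truth comes from 20,000 to 40,000 new patients.

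| Candidates (true factors, odds ratio) | Screened interactions | Cohorts | Slope: jackknife / true | c: jackknife / true |
|---|---|---|---|---|
| 30 (20, 1.6) | 20 | 6 | 0.93 / 0.92 | 0.741 / 0.739 |
| 36 (18, 1.5) | 30 | 75 | 0.92 / 0.87 | 0.708 / 0.698 |
| 30 (20, 1.3) | 20 | 25 | 0.88 / 0.81 | 0.641 / 0.631 |
| 36 (12, 1.3) | 0 | 182 | 0.88 / 0.78 | 0.613 / 0.601 |
| 36 (12, 1.3) | 30 | 68 | 0.88 / 0.69 | 0.616 / 0.593 |
| 60 (10, 1.3) | 60 | 25 | 0.87 / 0.59 | 0.620 / 0.582 |

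A separate set with 36 candidates and 0 to 55 screened interactions was milder: jackknife slope 0.96 against a true 0.93 to 0.91, with c overstated by 0.007 to 0.011. The last row of the table is an extreme case, with c overstated by 0.620 − 0.582 = 0.038. Elsewhere the overstatement is about 0.00 to 0.02.

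**4. The stated measure in the same runs.** In the extreme case percent correct was 72.3% by jackknife and 71.7% in new patients, a gap of 0.6 points, while the slope fell to 0.59. In a separate check with 36 candidates the overstatement was 0.3 to 1.0 points, about the size of the 0.9-point sampling error. With odds ratios of 1.3, percent correct was about the same as calling everyone event-free.

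**5. Does repeating the selection help?** In the milder set, a bootstrap repeating every step gave slopes of 0.934, 0.923 and 0.906 against true values of 0.926, 0.920 and 0.906. A jackknife that repeated the selection gave about 0.77 against 0.78 with 36 candidates and no interactions, and was noisier with interactions. Ten-fold cross-validation repeating the selection gave 0.91 against 0.92 with strong effects. With weak effects it gave 0.68 against 0.83 and 0.68 against 0.78, so it was too pessimistic there, though on only 6 to 8 cohorts.

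**6. What the 500 can resolve.** The Hanley–McNeil variance, with n₁ = 140, n₀ = 360, P₁ = c/(2 − c) and P₂ = 2c²/(1 + c), is [c(1 − c) + (n₁ − 1)(P₁ − c²) + (n₀ − 1)(P₂ − c²)]/(n₁n₀).
- c = 0.70: P₁ = 0.538, P₂ = 0.576, SE = 0.027
- c = 0.78: P₁ = 0.639, P₂ = 0.684, SE = 0.025

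The SE of the calibration slope in the same sample is about 0.13 to 0.21, for a standard deviation of the linear predictor from 1.0 down to 0.5.

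**7. Meaning for a displayed risk.** With the mean risk kept at 28%, corrected logit = logit(0.28) + slope × [logit(displayed) − logit(0.28)]. For a displayed 70%, the bracket is 0.847 + 0.944 = 1.791.
- slope 0.92: −0.944 + 1.648 = 0.704, or 67%
- slope 0.70: −0.944 + 1.254 = 0.310, or 58%

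**The case against.** The strongest reply is that the article never says the terms are frozen. What is repeated inside each resample is ordinarily left to a full protocol or analysis plan, neither of which is shown. That stands: frozen selection is an inference from the order of the steps. It is also fair that only the interaction screen is explicitly significance-based and that it is limited to clinically indicated pairs. Selection of main effects is merely implied, and the simulations supply it by assumption. What the reply does not reach is what the article does fix: percent correct as the sole named measure for this step, and storage of the model coefficients with no correction mentioned.

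A second reply is that the 500 held-out participants are untouched by selection, and that 140 deaths exceed the article's minimum of 100. They are indeed unbiased, and the article leaves open which measures will be used on them. But an overstatement of up to 0.02 in c is below one standard error there, and no correction of the coefficients is tied to that result.

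Three stronger readings are tempting and not supported:
- A reader might infer that a jackknife cannot capture selection because each fit shares 2499 of 2500 participants. That fails: a jackknife that repeats a programmable rule does capture it, as step 5 shows.
- A reader might infer that the jackknife makes the coefficients too extreme. It only assesses them. Extremeness comes from selection and unshrunk fitting, and would be the same under a bootstrap used only for assessment.
- A reader might infer that the gain from geriatric factors will be overstated. Nothing says that gain will be read from the jackknife.

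**Conclusion.** The point holds in limited form. Without any assumption about frozen terms, the named measure is poorly suited to its purpose: it barely registers overfitting, is matched at 72% by calling everyone a survivor, and does not measure the hypothesised gain in discrimination. No shrinkage is stated before the coefficients are stored.

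Conditionally, if the selected terms are held fixed in each jackknife fit, the internal estimate keeps the selection optimism. Under the assumed settings c is overstated by about 0.00 to 0.02 (0.04 in the one extreme case), and the slope reads 0.87 to 0.96 against a true value from about 0.92 down to 0.7 or lower. Strong effects with few candidates make the problem negligible; weak effects with many screened terms make it material. These figures rest on assumed candidate counts and effect sizes, on backward elimination, and on logistic models standing in for the time-to-event models. This is a worthwhile improvement to the plan, not a flaw that undermines the study.

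**What to change.** Before modelling starts:

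1. Write the selection of factors, functional form and interactions as a rule that a program can carry out. Clinical judgement enters by listing the eligible interactions in advance.
2. Repeat the whole rule in every resample, preferably a bootstrap of, for example, 500 resamples. A jackknife repeating the rule is possible but was noisier when interactions were screened.
3. Report the optimism-corrected c-statistic and calibration slope for each outcome, in place of percent correct or beside it.
4. Multiply the coefficients by the corrected slope, re-estimate the intercept or baseline, and only then store them in the application.

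The cost is analysis-plan wording, a pre-written selection rule, computing time and slightly lower reported performance. No new data are needed, and the 500 can stay as the held-out check.

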## Background

Among patients hospitalized for acute myocardial infarction (AMI), one-third are 75 years or older [1]. The number of incident AMI cases in this age group is expected to double over the next 30 years as the mean age of the general population increases [2], yet this group has been under-represented in AMI clinical trials and epidemiologic studies [3]. This group is fundamentally different from younger patients with AMI: they have a higher burden of comorbid diseases and aging-related physical and cognitive impairments, as well as lower physiologic reserve. Results from studies of younger patients with AMI may therefore not be directly applicable to this growing population.

While advanced age is a risk factor for adverse outcomes after AMI [1], there is great heterogeneity among older patients and chronological age is a relatively crude indicator of physiological age [3,4]. Despite emerging interest in understanding the role of geriatric conditions (such as physical and cognitive impairments) as they pertain to cardiovascular outcomes [3], the majority of studies examining risk have used administrative datasets that lack this information [5], and none of the currently available risk stratification tools for AMI incorporate geriatric conditions. Furthermore, these risk models have only modest discrimination in older patients [6,7], and were designed solely to predict clinical events (i.e., mortality, reinfarction) rather than patient-centered outcomes, such as health status.

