The Comprehensive Evaluation of Risk Factors in Older Patients with AMI (SILVER-AMI, R01HL115295, PI [name]) study was designed to address these knowledge gaps by melding principles from geriatrics and cardiology with the goal of more precisely characterizing the risk of traditional clinical events, as well as patient-centered outcomes, in older adults with AMI. The primary objective is to generate risk models that predict all-cause readmission, all-cause mortality, and decline in health status, that exceed the capabilities of currently available risk models in older adults. We hypothesize that the incorporation of geriatric conditions will lead to better discrimination than existing risk models. Secondary objectives are to: (1) estimate the frequency and determinants of adverse post-hospital events important in this population, including medication side effects, symptoms, falls, and bleeding; and (2) describe AMI processes of care (e.g. door-to-balloon time, revascularization strategies, use of secondary prevention medications). We believe that achieving these objectives can inform complex post-AMI decision-making in older adults (Figure 1). The purpose of this article is to describe the design, rationale, and methods of the SILVER-AMI study.

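### The hypothesis is better discrimination than existing risk models, but the only predictive-accuracy measure stated is percent correctly classified, which does not by itself test it

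*Protocol article*

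**What the plan says.** The Background of the protocol article sets a comparative aim. The primary objective is to build models "that exceed the capabilities of currently available risk models in older adults", and the hypothesis is explicit about the property in question: "We hypothesize that the incorporation of geriatric conditions will lead to better discrimination than existing risk models". The motivation is of the same kind: "these risk models have only modest discrimination in older patients".

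The Statistical analysis section describes evaluation in three places:

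- Model checking: "Models will be evaluated with an examination of residuals and goodness-of-fit statistics", with "statistical significance defined as a two-sided p-value <0.05".
- Internal validation: "jackknife methods [28] will be used to evaluate the percent of correct classification".
- External validation: "external validation will be performed on the 500 randomly selected participants", with no performance measure named.

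The Sample size and power section bases power on the relative risks of single explanatory variables. For the event rates, "we posited outcome rates of 39% and 28% for all-cause readmission and mortality", and decline in health status is assumed in 35% of survivors.

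**The concern.** The hypothesis concerns discrimination, relative to existing models. Discrimination is the ability of a model to rank patients who have the event above those who do not. Percent correct is a different quantity. It first turns each predicted risk into a yes or no at some cut-off, then counts agreements. Its value therefore reflects the cut-off and the event rate as well as the ranking. The article gives no cut-off, and the planned product reports a probability rather than a class.

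The other stated checks do not fill the gap, because residuals and goodness-of-fit statistics assess fit. The stated analysis also has no comparator, neither an existing score nor the study's own model with the geriatric variables left out. At stake is whether the reported results would bear on the study's main claim. A percent-correct figure alone could look respectable with no discrimination behind it, or look poor for a model that discriminates reasonably well.

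**Working it through.** **Inputs from the Sample size and power section.** Event rates of 28% (mortality), 39% (readmission) and 35% of survivors (health-status decline); development cohort 2500; validation cohort 500; relative risk 1.3 for the time-to-event outcomes; predictor prevalence 30% to 50%; power 90%.

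**Assumptions, not in the article.** AUC values of 0.60 to 0.75, because the article calls existing models modest but gives no C-statistic. Two illustrative cut-offs, 0.5 and the event rate, because none is stated.

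**Step 1: the plan's own figures.** Validation deaths: 500 × 0.28 = 140, as stated. Power for mortality: 2500 × 0.28 = 700 events. Schoenfeld's formula with hazard ratio 1.3 and two-sided 0.05 gives 88.9% at 30% prevalence and 93.5% at 50%. For readmission (2500 × 0.39 = 975 events) it gives 96.4% and 98.4%. The stated 90% is reproduced to within about 2 points at its lowest. It is power for a single predictor's effect, not for a gain in discrimination.

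**Step 2: percent correct as a function of AUC.** Take a calibrated equal-variance binormal model with separation d = √2 × z(AUC) and event rate π. A predicted risk above cut-off t corresponds to a score above

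c = [ln(t/(1−t)) − ln(π/(1−π)) + d²/2] / d.

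Then sensitivity = 1 − Φ(c − d), specificity = Φ(c), and percent correct = π × sensitivity + (1 − π) × specificity.

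Mortality at AUC 0.75: d = 1.414 × 0.6745 = 0.954.

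- Cut-off 0.5: c = (0 + 0.944 + 0.455)/0.954 = 1.467, sensitivity 0.304, specificity 0.929. Percent correct = 0.28 × 0.304 + 0.72 × 0.929 = 75.4%.
- Cut-off at the event rate: the two log terms cancel, so c = d/2 = 0.477 and sensitivity = specificity = 68.3%. Percent correct = 68.3%.
- Calling everyone a survivor: 1 − 0.28 = 72.0%, with no discrimination at all.

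| Outcome (event rate) | Nobody has the event | AUC 0.60 | AUC 0.65 | AUC 0.70 | AUC 0.75 | Gain, 0.65 to 0.75 |
|---|---|---|---|---|---|---|
| Mortality (28%), cut-off 0.5 | 72.0% | 72.0% | 72.4% | 73.5% | 75.4% | 3.0 points |
| Health status (35%), cut-off 0.5 | 65.0% | 65.3% | 66.6% | 68.8% | 71.7% | 5.0 points |
| Readmission (39%), cut-off 0.5 | 61.0% | 61.9% | 64.0% | 66.9% | 70.1% | 6.1 points |
| Any outcome, cut-off at event rate | as above | 57.1% | 60.7% | 64.5% | 68.3% | 7.6 points |

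Gains are taken from unrounded values. A different model for mortality, logistic with a normal linear predictor, gives 72.4%, 73.5% and 75.3% at AUC 0.65, 0.70 and 0.75 with a cut-off of 0.5, so the result does not hinge on the binormal form.

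**Step 3: what the table shows.** For mortality at a cut-off of 0.5, a model with AUC 0.60 scores no better, to one decimal, than the rule with no discrimination. With the cut-off at the event rate, a model with AUC 0.75 scores 72.0 − 68.3 = 3.7 points below that rule. The same model's score differs by 75.4 − 68.3 = 7.1 points according to a cut-off that the article does not give.

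**Step 4: is a C-statistic usable at the planned size?** The Hanley–McNeil standard error at an assumed AUC A = 0.70 uses Q1 = A/(2−A) = 0.538 and Q2 = 2A²/(1+A) = 0.576. With 140 deaths and 360 survivors, SE = √{[A(1−A) + 139(Q1−A²) + 359(Q2−A²)]/(140 × 360)} = 0.027, so the 95% CI is about ±0.054. With 700 and 1800 in the development cohort, SE = 0.012, about ±0.024. This ignores censoring. The precision of a paired difference also needs the correlation between the two scores, which the article does not give.

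**The case against.** The strongest reply is that this is a condensed article. Naming the comparator score, the index and its confidence interval is commonly left to a full protocol or analysis plan, and neither is shown. The measure for the 500 held-out participants is left open rather than fixed wrongly. Percent correct is tied only to jackknife internal validation, which the section presents as a check on reproducibility, and nothing there rules out a C-statistic. This stands in part: had the article been silent, there would be no point to raise. But it is not silent. It selects one accuracy measure, and that measure does not match its own hypothesis.

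Several stronger readings are tempting and are not supported:

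- A reader might infer that percent correct hardly responds to discrimination, so that a real gain would be invisible. That picture comes from mortality at a cut-off of 0.5. The other outcomes gain 5 to 6 points over the same AUC range, and every outcome gains 7.6 points with the cut-off at the event rate.
- A reader might infer that the study cannot confirm or refute its objective. A C-statistic can be computed from the planned models' predicted risks, and the article does not forbid it.
- A reader might call percent correct the only performance measure. Residuals and goodness-of-fit statistics are also stated; they assess fit, not discrimination.
- A reader might press the point that six-month status is unknown for participants censored early. No dropout rate is given, and the Events review section describes record-based ascertainment of readmissions and deaths, so the size of this cannot be judged.

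**Conclusion.** The concern holds as a mismatch between hypothesis and stated measure. Percent correct depends on an unstated cut-off and on the event rate, and a rule with no discrimination can match or beat a discriminating model. It therefore does not by itself test the hypothesis in the Background, and no other stated analysis does.

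The size is best shown by mortality: 72.0% for a rule with no discrimination, against 75.4% or 68.3% for the same AUC 0.75 model, depending on the cut-off. The direction of that comparison is not even fixed. The response to a rise in AUC from 0.65 to 0.75 ranges from 3.0 to 7.6 points across outcomes and the two cut-offs.

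These figures rest on the article's event rates, on assumed AUC values and cut-offs, and on a calibrated binormal model. The mismatch itself rests on the text alone.

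**What to change.** In the Statistical analysis section:

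1. Replace percent correct with an optimism-corrected C-statistic for internal validation. For the time-to-event outcomes, use a version that handles censoring and, for readmission, competing death.
2. Name the same measure for the 500 held-out participants.
3. State the test of the Background hypothesis as the difference in C with a 95% CI, in the same participants, between the full model and the model without geriatric variables. For mortality and readmission, add the same comparison against an existing score where an applicable one can be computed from the collected data. Health-status decline needs only the first comparison, because the Background says that existing models were designed solely for clinical events.

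The cost is analysis programming and wording; the comparison without geriatric variables needs no new data. Whether a particular existing score can be computed has to be checked once it is named. Calibration measures would be a useful optional addition but are not needed to repair this mismatch.

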Third, there are several specific products that will be developed from the data collected in SILVER-AMI. These include separate risk models for three outcomes (readmission, mortality, and decline in health status) that, once created, will be adapted for PC-based and smartphone use, similar to the Framingham Risk Calculator [36] or TIMI Risk Score [37]. Such decision aids may help to identify patients in need of resource intensive post-hospital interventions and therefore lead to improvements in real-time decision making at the point of care.

Finally, the recruitment network for SILVER-AMI includes approximately 70 sites across the U.S. in a variety of geographic settings. The network involves a large range of hospital sizes, as well as a mixture of academic and community hospitals, ensuring a diverse mixture of patients and practice patterns that will lend external validity to our findings. This network also has the potential to be used in future epidemiologic studies of other cardiac conditions, or for trials of interventions aimed at improving outcomes among older adults.

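### A random 500 drawn from the study's own cohort is labelled external validation; it is split-sample internal validation, and a fairly noisy one

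*Protocol article*

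**What the plan says.** The Statistical analysis section introduces two kinds of check with one purpose: "Internal and external validation techniques will then be used to test the reproducibility of the risk stratification tools". For the internal part, "jackknife methods [28] will be used to evaluate the percent of correct classification". For the other part, "external validation will be performed on the 500 randomly selected participants who were excluded from both model building and internal validation".

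The Sample size and power section says where the 500 come from: "Of the SILVER-AMI cohort of 3000 participants, 2500 participants will serve as the development cohort", and "500 will be randomly selected as the validation cohort". It justifies that number by a minimum of 100 outcome events and expects 140 deaths. The article names no other cohort, held-out hospital, region or later enrolment period for validation.

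**The concern.** External validation normally means testing a model on patients who differ from the development set in place, time or source. Patients allocated at random from one cohort differ from the rest only by chance. They come from the same network of about 70 hospitals (Study sites section), meet the same criteria (Table 1), and are measured with the same instruments on the same timetable (Table 2). A model that exploits something peculiar to these hospitals or to this period would do as well in the 500 as in the 2500, so the check cannot detect that failure.

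What is at stake is the wording of the eventual claim. If the results are reported under the plan's label, readers would credit the models with evidence of transportability that the design does not produce. A second, smaller matter is efficiency: one-sixth of the cohort (500/3000 = 16.7%) is kept out of model fitting for a check that gives a wide interval.

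**Working it through.** **Inputs from the protocol article.** Cohort 3000, development 2500, validation 500; mortality 28% ("we posited outcome rates of 39% and 28% for all-cause readmission and mortality"); relative risk 1.3 for time-to-event outcomes; predictor prevalence 30% to 50%; two-sided 0.05.

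**Assumption.** The article gives no C-statistic. I take 0.70 and show 0.65 to 0.80. Mortality is treated as binary at six months, without censoring.

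**1. The plan's own figures.**
- Deaths in the validation set: 500 × 0.28 = 140, as stated.
- Deaths in the development set: 2500 × 0.28 = 700.
- Schoenfeld power is Φ(ln(HR) × √(d·p(1−p)) − 1.96). With d = 700 and p = 0.30: 0.2624 × √147 = 3.181, less 1.96 = 1.221, so power is 88.9%. With p = 0.50 it is 93.5%. The stated 90% is reproduced to within about one point at its worst case.

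**2. Precision of C in the 500.** The Hanley-McNeil variance is [A(1−A) + (n₁−1)(Q₁−A²) + (n₀−1)(Q₂−A²)] / (n₁n₀), with Q₁ = A/(2−A) and Q₂ = 2A²/(1+A). At A = 0.70, Q₁ = 0.5385 and Q₂ = 0.5765.
- 500 participants (140 deaths, 360 survivors): (0.21 + 6.74 + 31.04)/50,400, so SE = 0.0275 and the half-width is 1.96 × 0.0275 = 0.054.
- 3000 participants (840 deaths, 2160 survivors): (0.21 + 40.66 + 186.69)/1,814,400, so SE = 0.0112 and the half-width is 0.022.

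| Assumed C | Half-width, n = 500 | Half-width, n = 3000 |
|---|---|---|
| 0.65 | 0.056 | 0.023 |
| 0.70 | 0.054 | 0.022 |
| 0.75 | 0.051 | 0.021 |
| 0.80 | 0.047 | 0.019 |

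The ratio is about √6 = 2.4 throughout. The n = 3000 column is sampling error only; an apparent C from the fitting data must also be corrected for optimism.

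**3. Calibration in the 500.** For observed/expected deaths, SE of the log ratio = √((1−0.28)/(500 × 0.28)) = 0.0717, giving 95% limits of about 0.87 to 1.15.

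**4. Cost to development.** Using all 3000 gives 3000 × 0.28 = 840 deaths. Power at p = 0.30 becomes Φ(3.485 − 1.96) = 93.6% instead of 88.9%; at p = 0.50 it becomes 96.7% instead of 93.5%. The gain is 3 to 5 percentage points.

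**The case against.** The plan's defence is a fair one in several respects.

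- **The declared aim is reproducibility, not transportability.** A random hold-out can test reproducibility, and the article says openly that the 500 are randomly selected. This stands. It limits the point to the label and to what may be claimed. It does not rescue the label, because reproducibility within the same population is what internal validation shows.
- **The size passes the article's own criterion.** The 140 expected deaths exceed the 100-event minimum, and an untouched hold-out is protected from data-driven selection. Both are true, so calling the check noisy is a judgement about interval width, not a breach of the plan's rule.
- **Little is lost to fitting.** The plan already resamples the 2500, where the C half-width at 0.70 would be about 0.024 (SE 0.0123), close to the 0.022 at 3000. This stands.

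Three stronger readings are tempting but unsupported.

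- A reader might take the Discussion's phrase "ensuring a diverse mixture of patients and practice patterns that will lend external validity to our findings" as a claim resting on the split. It concerns the diversity of the hospital network.
- A reader might conclude that the hypothesis of better discrimination than existing models would be tested with too little power in the 500. The article does not schedule that comparison there.
- A reader might infer that the handheld application would be released on the strength of the external label. The article says only that applications follow once the final models exist.

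**Conclusion.** The concern holds in a limited form. The label is wrong on the article's own description, and this needs no assumption beyond random selection from one cohort. The 500 can speak to reproducibility but not to performance at other hospitals or at other times.

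The check is also wide: about ±0.054 on the mortality C-statistic, or ±0.047 to ±0.056 over assumed values of 0.80 to 0.65, roughly 2.4 times the sampling half-width with all 3000. These figures rest on the posited 28% mortality, an assumed C and a binary-outcome approximation. The loss to model development is modest (140 expected deaths and 3 to 5 points of power). This should be corrected, but it does not undermine the models themselves.

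**What to change.** **Minimum.** In the Statistical analysis section, rename the random split *internal (split-sample) validation* and make no external-validation claim from it. This costs only wording.

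**If an external claim is wanted from the existing data**, choose one of two routes in advance:

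1. Draw the validation set of about 500 as whole sites or as the last-enrolled period instead of at random. The cost is more variable estimates, because few sites or one period carry the check.
2. Develop on all 3000, correct optimism with a bootstrap that repeats every selection step (predictors and interactions) in each replicate, and add internal-external cross-validation that leaves out groups of sites or regions in turn. The cost is computing time and the loss of an untouched hold-out.

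Neither route needs new patients or new data. Under either, report discrimination and calibration with confidence intervals.
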